## Supplemental Appendix 1

### Trials Protocols

#### SAAF-T

##### A. SPECIFIC AIMS

In this proposal, we request funding to conduct a randomized prevention trial to test the SAAF–HS program’s efficacy. The sample will include ~500 rural African American families with a 10th-grade student, half of whom will be assigned randomly to a SAAF–HS and half to an attention-control group. Pre-intervention, post-intervention, and long-term follow-up assessments of adolescents’ substance use and high-risk sexual behavior will be gathered from the entire sample.

Our specific aims are as follows:

1. To test the hypothesis that rural African American adolescents randomly assigned to participate in SAAF–HS, compared to attention-control participants, will demonstrate lower rates of substance use initiation, and that those who already use substances (e.g., cigarettes; alcohol, including binge drinking; marijuana and other illicit substances) will use them less frequently and consume lower quantities at each follow-up assessment.
2. To test the hypothesis that rural African American adolescents randomly assigned to participate in SAAF–HS, compared to attention-control participants, will demonstrate lower rates of high-risk sexual behavior (e.g., instances of unprotected sexual intercourse, multiple sexual partners) at each follow-up assessment.

##### D. RESEARCH METHODS

###### D.1. Participants

A random sample of 500 rural African American families with a son or daughter in the first semester of 10th grade in a public high school will participate in the study.

###### ***D.1.1. Eligibility, Random Assignment, and Contamination***

Lists of all African American 10th-grade students will be obtained from each of the 6 participating high schools. The students on each school’s list will be randomly ordered to determine the sequence in which families will be contacted to be screened for eligibility. A small number of students will be excluded from the pool of potential participants. If the primary caregiver or adolescent does not speak English, which is unlikely, the youth will be excluded. Twins and stepsiblings who both are in the 10th grade will be excluded because the inclusion of more than one participant from the same family introduces confounds that make interpretation difficult. Youth from families who have taken part in any of the investigators’ other studies will also be excluded. Although this is unlikely because participants for the proposed study will not be recruited from counties that were sampled for previous research, some participants may have moved to one of the targeted counties.

Enrolled families will be assigned randomly to either the SAAF–HS or attention-control condition (see recruitment procedures, section D.1.2). All families will be followed across the course of the proposed study and assessed regardless of the number of SAAF–HS or attention-control sessions they do or do not attend (an intent-to-treat analysis); this includes youth who drop out of school during the study.

###### ***D.1.2. Family Recruitment and Retention Strategies***

The recruitment process will be conducted in the following sequence: (1) a letter from the school principal will be mailed to parents/ guardians informing them of the study; (2) a community liaison will visit the families’ homes to determine their eligibility; and (3) eligible families will be invited to participate, with active consent obtained from primary caregivers and active assent from adolescents.

***D.1.2a. Principals’ letter.*** Each primary caregiver of an African American 10-grade student who is selected randomly from the pool of potential participants will receive a letter from the school principal describing the study and the school’s collaboration with the University of Georgia (UGA). Caregivers will be informed that they will be contacted by representatives associated with UGA (community liaisons), that they and their 10th-grade son or daughter may be invited to participate, and that participation is voluntary.

***D.1.2b. Community liaisons’ home visit.*** Community liaisons will schedule home visits to students’ families based on the randomly permuted order of the school list. During this visit, the liaison will describe the study to

the caregiver and student and tell them that, based on their responses to the screening questions (English-speaking, no siblings in the same grade, no prior participation in investigators' research), they may be eligible to participate. Adolescents and caregivers who do not meet any of the exclusionary criteria will be invited to participate in the study and will be informed of its requirements: active consent from a primary caregiver for his or her own participation and for the adolescent's participation; active assent from the adolescent for his or her own participation (consent forms can be found in Appendix D); random assignment to either the prevention or attention-control group; completion of questionnaires three times during an 18-month period; and caregivers' and students' participation in the prevention or attention-control program. A family will be classified as refusing at this point if either the caregiver or student does not wish to take part in the study.

**D.1.2c. Monetary incentives.** At each pretest, posttest, and follow-up assessment in the proposed project, each adolescent will receive a \$50 gift certificate to a local department store and each primary caregiver will receive a \$100 honorarium.

**D.1.2d. Retention.** Following each data collection home visit and prevention session, community liaisons contact participants to inquire about the quality of the experience and to answer questions. Between data collections, liaisons call families on a regular basis and visit the homes of families whose telephone service has been interrupted. The families also provide contact information for three individuals who will always know their whereabouts; these lists are updated at each home visit. All families receive a semiannual newsletter that includes a stamped address correction form to facilitate the updating of address lists before post office forwarding orders expire.

## **D.2. Overview of the Prevention and Research Procedures**

All prevention and attention-control families will participate in a pretest, a posttest, and a long-term follow-up assessment 9 months after the posttest. Both prevention and attention-control families will participate in a 5-week intervention. The posttest data collection will take place 3 months after the interventions conclude to allow any transitory immediate effects to dissipate.

## **D.3. SAAF–HS Program Implementation**

### **D.3.1. Group Leaders**

Teams of three persons will lead the prevention and attention-control groups, each of which will include 10 to 12 families. All group leaders will be African Americans with a minimum of a bachelor's degree in psychology, nursing, education, social work, or a related field. The investigators will prepare a leaders' guide that will describe all facets of the delivery of the SAAF–HS and the attention-control program. The leaders will receive 30 hours of training on content delivery in a structured group process format, implementation of specific curriculum activities, guided practice in delivering and pacing curriculum segments, and leader self-care. Didactic material, role-playing exercises, and modeling will be used to teach the protocol for each session. Prior to completion of training, group leaders must demonstrate mastery of the curriculum by scoring 100% on a written examination covering the session material. Leaders will meet with the prevention coordinator each week to review the previous week's sessions and prepare for those in the coming week.

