### **D.8.2. Analyses for Aims 1 and 2: Primary Outcomes**

The primary issue to be addressed in Aims 1 and 2 is SAAF-HS's effectiveness in deterring the onset and escalation of substance use and high-risk sexual behavior across the 18 months separating the pretest and long-term follow-up assessments. A dramatic growth in substance use and high-risk sexual behavior is likely to occur across measurement points, which include the beginning of 10th grade, middle of 10th grade, and beginning of 11th grade. SAAF-HS's impact on each of the outcomes will be examined in three ways: on posttest (middle of 10th grade), on long-term follow-up (beginning of 11th grade), and on growth trajectories. The two single-time-point analyses will be conducted with Structural Equation Modeling (SEM) using the maximum likelihood method and controlling for baseline levels of substance use and high risk-sexual behavior. The first outcome analysis (posttest) identifies reduction in substance use and high risk-sexual behavior; the second (long-term follow-up) will be used for tests of delayed initiation and reduction of substance use and reduction of high-risk sexual behavior. We will explore, in an additional analysis, SAAF-HS's effects on delaying the onset of sexual intercourse. SAAF-HS, however, is likely to have its strongest impact on growth trajectories (Taylor et al., 2000). A baseline growth model with random intercepts and slopes will be established for the attention-control condition. A multigroup analysis will then be conducted, testing the equivalence of growth parameters between the attention-control and the SAAF-HS groups (Byrne, 2001). If the multigroup analyses detect differences between the slopes (rates of growth for substance use or high-risk sexual behavior) of the SAAF-HS and attention-control group, impact statements will be made by examining how the average substance use and sexual risk behavior trajectories change with time.

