### **D.8.6. Statistical Power**

In this section, we discuss statistical power for the models we described previously, including the SAAF–HS intervention’s impact on changes in the slopes of drug use and high-risk sexual behavior and on outcomes at a single point in time. In these calculations, we assume conservatively a 13% loss in data across time, yielding two groups of 250 participants in each condition. For growth models with either continuous or discrete outcomes, we have used power calculations that Brown and colleagues have made available on the internet (<http://psmq.usf.edu/products.html>) to determine the smallest effect size we can detect with 80% power for changes in the slope parameter, assuming linear growth over three time points. When the measurement reliability is 60%, we can achieve 80% power when the ES is 0.1 at posttest and grows to 0.2 at long-term follow-up. For conducting a test at a single time point on a continuous outcome, based on Cohen (1988), we can detect an effect size of 0.25 at 80% for a 0.05 level test, assuming negligible variation based on school. We also have calculated power by taking this factor into account. Based on variability observed in other preventive trials among schools and individuals (Brown and Liao, 1999) the power is 80% to detect an ES of 0.36 and 70% to detect an ES of 0.31 for 0.05 level tests. Thus, we clearly have adequate power to detect a moderate effect for continuous outcomes involving single time points. For a discrete measure at a single time point, such as a comparison of the proportion of individuals who are using a substance, we will be able to detect an odds ratio of at least 1.6 with 80% power using a 0.05 level chi-square test (Fleiss et al., 2003). This odds ratio corresponds to a reduction from 50% users to 38% in the intervention group.

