### D3. Prevention Development Plan

**D3.1. Development of the Prevention Program with the Assistance of Community Members:** Project staff will meet with two groups of 10 adults and two groups of 10 youths who are representative of the African American communities in the participating counties to discuss the prevention curriculum modules and the proposed training process. The focus group members will be asked for feedback about the propriety of the curriculum for rural African American families and emerging adults; the curriculum will be revised accordingly. The focus group will evaluate the revised curriculum to insure that the changes effectively addressed their suggestions.

A pilot intervention feasibility study will be conducted with a sample of 10 African American emerging adults and their parents. The pilot will be videotaped and a staff member from the Center will view the tapes and take notes on each session. Session logistics, as well as the relevance and appropriateness of activities and materials, will be assessed and any necessary revisions will be made to the final curriculum.

**D3.2. Implementation of the Prevention Program:** Procedures for recruiting and training the group leaders, insuring fidelity to the prevention curriculum, and engaging participating families will follow the same guidelines that [name] and [name] used successfully in SAAF ([name] et al, in press; [name] & [name], in press).

**D3.2a. Group leaders:** Three-person teams will lead prevention groups, each of which will include ~10 families. All group leaders will be African Americans. The leaders will receive 30 hours of training at the Center for Family Research of the University of Georgia. The training will address content delivery within a structured group process format, implementation of specific curriculum activities, guided practice in delivering and pacing curriculum segments, and leader self-care. Drs. [name], [name], [name], Brown, and [name], along with Prevention Coordinator [name], will prepare a leaders' guide. Didactic material, role-playing exercises, and modeling will be used to teach the protocol for each session. Prior to completion of training, group leaders must demonstrate mastery of the prevention programming by scoring 100% on a written examination covering

the prevention material. Leaders will meet with [name] for 2 hours each week to review the previous week's sessions and prepare for those in the coming week.

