**D6.1d. *Baseline equivalence for prevention and control groups:*** Before testing the hypotheses, we will use hierarchical linear modeling (HLM; Bryk and Raudenbush, 1992) to conduct statistical comparisons between prevention and control group members on all study variables. Because participants will be recruited from schools, we will use HLM to examine pretest differences among youths attending different schools. School-level effects will be included in tests of the hypotheses if they account for unique variance at baseline.

**D6.2. *Substance Use Outcome Measures:*** The assessment of substance use (see Section D5.8) covers initiation, escalation, and problem use. SAAF—EAP intervention effects will be examined for use, frequency of use, and quantity used during the past 30 days, 6 months, and 1 year. We can determine lifetime use for all

substances from the history-of-use questions, identifying movement from nonuse to initiation of use for specific substances. We will use discrete event-history models to examine SAAF-EAP effects on initiation over the 3 repeated measures.

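### Neither analysis plan models session-group clustering, so standard errors will be too small if families in the same group have correlated outcomes

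*Combined protocol and SAP*

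**What the plan says.** Delivery. SAAF-T D.3.1 puts both arms into groups: "Teams of three persons will lead the prevention and attention-control groups, each of which will include 10 to 12 families". SAAF-T D.5 gives the attention-control programme the same meeting structure as the intervention. AIM D3.2a groups the intervention arm only: "Three-person teams will lead prevention groups, each of which will include ~10 families". AIM controls receive mailed leaflets (D2, D3.3).

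Allocation. Both trials randomise families. SAAF-T D.1.1 says "Enrolled families will be assigned randomly to either the" intervention or the attention-control condition, and AIM D1.1 is equivalent.

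Analysis. SAAF-T D.8.2 says "The two single-time-point analyses will be conducted with Structural Equation Modeling (SEM) using the maximum likelihood method", adjusted for baseline. It adds growth models that vary between individuals, plus binary, count and zero-inflated models. None of these has a level or term for session group, leader team or school. AIM D6.4a specifies growth models that let individuals differ in rate of change, and names no session-group level. AIM D6.1d treats school conditionally: "School-level effects will be included in tests of the hypotheses if they account for unique variance at baseline".

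Power. SAAF-T D.8.6 says "we can detect an effect size of 0.25 at 80% for a 0.05 level test, assuming negligible variation based on school". Allowing for school variation, "the power is 80% to detect an ES of 0.36 and 70% to detect an ES of 0.31 for 0.05 level tests". AIM D6.3 makes no allowance for school or for session group.

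**The concern.** Families who attend the same group share leaders, group-mates and the way the sessions were run. Their later outcomes may therefore be correlated, and the documents give reason to expect some of this. AIM D1.2 excludes certain students because their presence in group activities might harm others. AIM D4.2 has leaders rate each group's engagement and supportiveness. Both trials build session fidelity into each participant's dosage score (SAAF-T D.6.2, AIM D4.2).

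A model that treats families as independent ignores this correlation. With a positive ICC, the variance of a treatment comparison exceeds what the model reports. Confidence intervals are then too narrow and the false-positive rate exceeds its nominal level. This affects the primary comparisons in both trials. In AIM the structure is one-sided, because controls have no groups.

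**Working it through.** **Inputs**

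- SAAF-T: 10 to 12 families per group, midpoint 11 (D.3.1), with a 13% loss (D.8.6). Analysed per group: 11 × 0.87 = 9.57. Both arms are grouped.
- AIM: about 10 families per group (D3.2a), with 15% attrition (D6.3). Analysed per group: 10 × 0.85 = 8.5. Prevention arm only.
- Test level 0.05. SAAF-T D.8.6 does not state sidedness; two-sided is assumed.
- Session-group ICC: not in the documents. Assumed values are .02, .05 and .10.

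SAAF-T D.8.6 states "we assume conservatively a 13% loss in data across time, yielding two groups of 250 participants in each condition", which does not fit about 500 enrolled families. That is a separate matter. The type I error below depends on group size, not on the total.

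**Step 1. The plan's own figure.** With 250 per arm, 80% power and two-sided 0.05, the detectable effect is (1.96 + 0.842) × √(2/250) = 2.802 × 0.0894 = 0.251. The stated 0.25 reproduces. The school-adjusted 0.36 implies a variance inflation of (0.36/0.2506)² = 2.06.

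**Step 2. Design effect for session groups.**

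- SAAF-T, both arms: DE = 1 + (9.57 − 1) × ICC.
- AIM, prevention arm: DE = 1 + (8.5 − 1) × ICC. With equal arms and variances, the inflation of the comparison is (DE + 1)/2.

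**Step 3. True type I error of the unadjusted test.** 2 × (1 − Φ(1.96/√inflation)). Example, SAAF-T at ICC .05: 1.96/√1.43 = 1.64, giving 0.101.

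| Assumed ICC | SAAF-T inflation | SAAF-T type I | AIM prevention-arm DE | AIM average inflation | AIM type I |
|---|---|---|---|---|---|
| .02 | 1.17 | 7.0% | 1.15 | 1.08 | 5.9% |
| .05 | 1.43 | 10.1% | 1.38 | 1.19 | 7.2% |
| .10 | 1.86 | 15.0% | 1.75 | 1.38 | 9.5% |

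Taking square roots, correct standard errors would be 1.08, 1.20 and 1.36 times the planned ones in SAAF-T, and 1.04, 1.09 and 1.17 times in AIM.

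**Step 4. Simulation check (4,000 runs, full groups, no attrition).** At ICC .01, .05 and .10:

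- SAAF-T, 23 groups of 11 per arm: 0.064, 0.108 and 0.164. The formula at m = 11 gives 0.062, 0.110 and 0.166.
- AIM, 18 groups of 10 in one arm: 0.055, 0.075 and 0.116. The formula at m = 10 gives 0.055, 0.077 and 0.104.

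Agreement is close, except that the simulation is somewhat higher for AIM at ICC .10.

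**Step 5. School.** Families were simulated as randomised across six schools and analysed without a school term. Type I error was 0.049 to 0.057 for school ICCs of .02 to .10. With arms balanced within school it was 0.047 falling to 0.039. Both are near or below nominal.

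**The case against.** **The ICC may be small.** This is the strongest reply, and the documents give no value. SAAF-T outcomes are self-reported privately at home, starting three months after the sessions end (D.2, D.6.1). Non-attenders stay in the analysis (D.1.1), which dilutes any group effect. SAAF-T has one meeting site per county, not separated by arm (D.3.3), so a site effect would largely cancel. All of this stands. It argues for conditional wording and a stated ICC range. It does not show that the ICC is zero.

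**SAAF-T already allows for clustering.** Its school-adjusted detectable effect of 0.36 exceeds the 0.251 × √1.86 = 0.34 needed at a session-group ICC of .10. That margin protects power, but it does not correct the standard errors of the analysis.

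**The published text may be incomplete.** SAAF-T section numbering passes from D.8.3 to D.8.6, and AIM D6.4a lists multilevel software among its options. The claim is therefore limited to the text available, which names no session-group level.

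**Stronger readings to avoid.**

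- A reader might infer that leaving out school also makes standard errors too small. With families randomised, school main effects are largely shared by the arms, and Step 5 shows no such inflation.
- A reader might take the 2.06 inflation implied by SAAF-T D.8.6 as clustering that the analysis ignores, and derive a large type I error from it. That section attributes the allowance to variability among schools and individuals. It does not say whether this includes variation of the treatment effect between schools, which would be needed to inflate the error.
- A reader might say that AIM's baseline school test has little power. AIM states six counties but not the number of schools, so this cannot be established.

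**Conclusion.** The point holds in conditional form. The available analysis text of both trials omits session-group clustering, and standard errors will be too small if the session-group ICC is positive. Over assumed ICCs of .02 to .10, the type I error of a nominal 5% test is about 7.0% to 15.0% in SAAF-T and 5.9% to 9.5% in AIM. AIM is less affected because only one arm meets in groups, and at ICC .02 its effect is slight. Incomplete attendance would lower all of these figures.

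The figures assume equal group sizes, a continuous outcome at a single time point and, in AIM, equal arms and variances. The growth, binary and count analyses share the omission, but their ICCs could differ.

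On school, the supportable criticism is narrower. AIM's rule is data-dependent and looks at baseline rather than outcome variance. SAAF-T allows for school in its power calculation but names no school term in its analysis. These are matters of prespecification and precision, not of understated standard errors.

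**What to change.** 1. Both trials: store a session-group identifier for every family assigned to a grouped programme. Families who attend nothing keep their assigned group, so the intent-to-treat set is unchanged.
2. SAAF-T D.8.2: make session group the cluster in the single-time-point and growth models, through a random effect or cluster-robust standard errors. At 250 families per arm there would be 250/12 to 250/10, about 21 to 25, groups per arm, which makes this feasible.
3. AIM D6.4: fit a partially nested model, with a random session-group effect in the prevention arm and each control family as its own cluster. Use a small-sample correction, since 185/10 gives only about 18 prevention groups.
4. Secondary: in AIM D6.1d, replace the baseline-test rule with a prespecified school term, and add one in SAAF-T D.8.2.
5. Report detectable effects over a stated session-group ICC range.

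The cost is a few lines of analysis text and one stored variable. The downside is somewhat wider intervals.
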